### Invasive ventilation

Direct tracheal intubation (without NIV trial) will be indicated if the patients also meet at least one of the following criteria: Hemodynamic instability [a systolic blood pressure (SBP) <80 mmHg or <40% of the basal or vasoactive drug requirements for more than 2 h is required to maintain the SBP above 80 mmHg]. Ventricular arrhythmias with hemodynamic instability or ECG signs of myocardial ischemia. GCS of less than 9. Sedation requirement due to agitation.

Tracheal intubation after 1 h of NIV will be indicated in patients meeting at least one of the following criteria: Severe hypoxemia (SpO_2_ < 92% with a FiO_2_ as prescribed according to the randomized group). Respiratory acidosis (pH <7.30 with a PaCO_2_ > 50 mmHg). Signs of distress with increased use of accessory respiratory muscles or paradoxical thoracic-abdominal respiratory movements.

### Study variables

The primary outcome of the iPROVE trial is a composite of pulmonary and systemic complications experienced by the study population in the first 7 days after surgery and can be divided into respiratory complications and systemic complications as discussed below.

Respiratory complications:Atelectasis: defined by a combination of SpO_2_ ≤ 96% during the air test and chest X-ray images suggesting lung opacities with a shift in the mediastinum, hilum, or hemidiaphragm toward the affected area and compensatory overinflation in the adjacent non-atelectic lung. Hypoxemia: defined as SpO_2_ of 92% or less with 0.21 FiO_2_ or SpO_2_ of 95% or less with 0.5 FiO_2_. ARDS: according to the Berlin definition [33]. Pneumonia: the presence of a new pulmonary infiltrate and/or progression of previous pulmonary infiltrates on a chest radiograph plus at least two of the following criteria: (a) leukocytosis with >12,000 WBC/mm^3^ or leukopenia with <4000 WBC/mm^3^, (b) fever >38.5°C or hypothermia <36°C, and (c) increased secretions with purulent sputum and a positive bronchial aspirate. Pleural effusion: chest x-ray with the presence of costophrenic angle blunting, displacement of adjacent anatomical structures, and blunting of the hemidiaphragmatic silhouette in the supine position. Bronchospasm: presence of expiratory wheezing treated with bronchodilators. Pneumothorax: air in the pleural space and the mediastinum is shifted to the opposite side (a thorax radiography will be performed in suspected cases of auscultation hoarseness). Aspiration pneumonitis: respiratory failure after the inhalation of regurgitated contents. Requirements for rescue maneuvers: increased FiO_2_, increased requirement for CPAP, or the need for noninvasive or invasive ventilation. Early extubation failure or requirement of reintubation.

Systemic complications: Heart failure: cardiac index <2.5 ml/min/m^2^ or >2.5 when ≥5 μg/kg/min dobutamine is required. Clinical signs (hypotension, oliguria, pulmonary edema) together with NT-proBNP >13 pg/ml or echocardiographic diagnosis [34]. Systemic inflammatory response syndrome (SIRS): axillary temperature >38.5°C or <35.5°C, or central temperature of 38°C and 36°C, respectively. Heart rate (HR) >90 bpm (in the presence of atrial arrhythmia, the ventricular rate measurement will be used). If medication that could affect the HR is administered, the patient must meet the following three criteria: (a) RR >20 rpm, (b) a PaCO_2_ of <32 mmHg or use of mechanical ventilation, (c) leukocytosis of ≥12 × 10^9^/l, or leukopenia of <4 × 10^9^/l. Sepsis: infectious focus identified plus SIRS criteria. Severe sepsis: sepsis plus at least one organ dysfunction, hypoperfusion, or hypotension. Septic shock: Severe sepsis with hypotension and hypoperfusion that is unresponsive to fluids. Renal failure, following the acute kidney injury scale [35]. Anastomosis dehiscence: suture line failure with leakage of the intraluminal contents that may cause peritonitis, fistula from the wound or drain, or appearing as an abdominal fluid collection (diagnosed with imaging) that causes fever, septicemia, and shock. Abdominal abscess diagnosed with imaging techniques (CT). Surgical wound infection: following the CDC criteria [36]. Surgical reintervention required.

The secondary outcomes are the composite of postoperative pulmonary complications at 7 days and over the first 30 post-surgical days. Other secondary outcomes are: Increased ICU length of stay (LOS). Increased hospital LOS. ICU readmission in the first 30 days after surgery. Hospital readmission in the first 30 days after surgery. Mortality within 30, 180, or 365 days. The presence of plasma inflammatory markers: increased expression of interleukin 8 (IL-8), tumor necrosis factor alpha (TNF-α), and monocyte chemo-attractant protein (MCP-1). Plasma samples will be taken preoperatively and 48 h post-surgery.

The primary and secondary data outcomes will be taken 15 min and 3 h after PACU/ICU admission and at 1, 2, 7, and 30 days after surgery, with a 180- and 365-day follow-up for mortality. Plasma samples will be taken preoperatively and at 2 days after surgery. If the patient is not extubated in the operating room, the first four data time points will be taken from the time of extubation.

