### Study population

The inclusion criteria of the study population consists of male and female patients ≥18 years old, with an intermediate or high risk of PPCs as defined by the ARISCAT score (based on the analysis of seven factors, in which a score between 26 and 44 points defines an intermediate risk and a score of more than 44 points defines a high risk [31]), with a body mass index (BMI) of <35 kg/m^2^, who are scheduled for major abdominal (laparotomy and laparoscopic) surgery with an expected operating time of more than 2 h (see Additional file 2). Exclusion criteria are age <18 years, pregnancy or breast-feeding, a body mass index of >35 kg/m^2^, moderate or severe acute respiratory distress syndrome (ARDS; PaO_2_/FiO_2_ < 200 mmHg), diagnosis of heart failure defined as a cardiac index <2.5 ml/min/m^2^ or >2.5 when ≥5 μg/kg/min dobutamine is required, or suspicion of heart failure according to clinical signs (hypotension, oliguria, pulmonary edema) together with NT-proBNP >13 pg/ml, diagnosis or suspicion of intracranial hypertension (>15 mmHg), mechanical ventilation in the last 15 days (including CPAP), presence of pneumothorax or giant bullae on a chest radiograph or computed tomography (CT), patients with chronic obstructive pulmonary disease (COPD) requiring oxygen or CPAP, and patients participating in another interventional study.

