#### Standard group

The patients will be ventilated as previously described in the General intraoperative ventilator management section.

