#### Individualized group

In this group, an ARM is performed after intubation followed by a PEEP titration trial. Before the recruitment is performed the anesthesiologist must ensure that there is hemodynamic stability [mean arterial pressure (MAP) of more than 70 mmHg and/or a cardiac index of more than 2.5 ml/min/m^2^] for at least 5 min, a stroke volume variation (SVV) of less than 10%, and an adequate neuromuscular blockade (0 of 4 by TOF). The ARM is performed as described in the following section.

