### Alveolar recruitment maneuver (ARM)

The ventilator will be changed from VCV to pressure-controlled ventilation (PCV) with a 20-cmH_2_O driving pressure and an RR of 15 breaths per minute (rpm), I:E of 1:1, 0.8 FiO_2_, and PEEP of 5 cmH_2_O. For the recruitment phase, the PEEP level will be increased in steps of 5 cmH_2_O every ten respiratory cycles, up to a PEEP of 20 cmH_2_O, to produce an airway opening pressure of 40 cmH_2_O and maintained for 15 respiratory cycles in the opening pressure [32] (total maneuver time: 180 s). If hemodynamic instability appears during the recruitment phase (a >50% decrease in the cardiac index or MAP), the maneuver will be interrupted and 5–15 mg ephedrine or 0.05-0.15 mg phenylephrine given; after hemodynamic stabilization, a new ARM will be performed. After lung recruitment is accomplished, the optimal PEEP is titrated through a decremental PEEP trial, as described in the following section [8] (Figure 2).

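### The pneumothorax component requires mediastinal shift, so it under-counts barotrauma; the effect on the primary composite is small, but the harm reading of the recruitment-maneuver arms is weakened

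*Protocol article*

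**What the plan says.** Under Study variables, the protocol article lists the respiratory complications that enter the 7-day primary composite. One entry defines pneumothorax as "air in the pleural space and the mediastinum is shifted to the opposite side". Imaging for this component depends on clinical suspicion: "a thorax radiography will be performed in suspected cases of auscultation hoarseness".

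The arms differ in exposure to high airway pressure. For the individualized intraoperative strategy, "In this group, an ARM is performed after intubation followed by a PEEP titration trial". The maneuver raises PEEP stepwise "to produce an airway opening pressure of 40 cmH_2_O and maintained for 15 respiratory cycles in the opening pressure". A second maneuver follows once the best compliance is known. Further ones may follow the 40-minute checks, accidental depressurization, suction before extubation, or intraoperative hypoxemia. For the standard strategy, "The patients will be ventilated as previously described in the General intraoperative ventilator management section". That section prescribes no recruitment maneuver for the standard arms, and their intraoperative rescue raises FiO2 and then PEEP, again without one.

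The same list of respiratory complications also counts hypoxemia, the need for rescue (more FiO2, more CPAP, noninvasive or invasive ventilation) and reintubation. No other component names air leak, and drain insertion is not mentioned.

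**The concern.** The two conditions are joined by *and*. Read as a scoring rule, pleural air on a film without contralateral shift fails the pneumothorax component, even if a drain is placed. The neighbouring entries for atelectasis and pleural effusion are also built from joint criteria, so this reads as deliberate structure and not loose description.

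Pneumothorax is the listed complication most directly tied to possible harm from the strategy under test. Two of the four arms have repeated exposure to 40 cmH2O and two have none by protocol. If the maneuver causes air leaks, this component should show it, and the definition reduces its ability to do so. The pulmonary composites at 7 and 30 days share the gap if they use the same entry. So does the interim test for benefit or harm, which is run on the main endpoint.

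**Working it through.** **1. The plan's own figures.** Under Statistical analysis the assumed risk is 25% and the relative reduction 50%, so the planned difference is 25% − 12.5% = 12.5 percentage points. The stated 230 per arm reproduces if the 5% level is split over the six pairwise comparisons of four arms, which is an assumption because the article does not name the adjustment:

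n = (z₁₋α/₂ + z₀.₈₀)² × [p₁(1−p₁) + p₂(1−p₂)] / (p₁−p₂)², with α = 0.05/6

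= (2.638 + 0.842)² × (0.1875 + 0.1094) / 0.0156 ≈ 230.1, rounded up to 231 (235 with pooled variance).

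Then 4 × 230 = 920; 920 × 1.10 = 1012; 1012/4 = 253 per arm; 2 × 253 = 506 in the two individualized intraoperative arms. These figures do not decide a point about a definition, but they give the scale to judge it by.

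**2. Which cases are lost.**

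| Case | Pneumothorax component | Composite |
|---|---|---|
| Pleural air with contralateral shift | counted | counted |
| No shift, but hypoxemia, rescue, ventilation or reintubation | not counted | counted through the other component |
| No shift, no other component met (drained or not) | not counted | not counted |

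The composite loses only the third row. The component loses the second and third.

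**3. Size at composite level.** The article gives none of the three inputs needed, so all are assumed: *p*, pneumothorax incidence in the individualized arms (0.2% to 2%); *s*, the share without shift (50% to 100%); *c*, the share of those that meet no other component (25% to 100%). The understatement of composite risk is u = p × s × c.

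| p | s | c | u (percentage points) | Missed per arm of 253 | Missed over 506 |
|---|---|---|---|---|---|
| 0.2% | 50% | 25% | 0.025 | 0.06 | 0.13 |
| 0.5% | 80% | 50% | 0.2 | 0.51 | 1.01 |
| 1% | 80% | 50% | 0.4 | 1.01 | 2.02 |
| 1% | 80% | 100% | 0.8 | 2.02 | 4.05 |
| 2% | 100% | 100% | 2.0 | 5.06 | 10.12 |

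At the extreme, a true risk of 14.5% would be recorded as 12.5%. The bias in a contrast between arms is the difference between their values of u. The table therefore gives an upper figure for the contrast, with no loss at all in the comparator. If incidence, share without shift and capture were the same in all arms, the bias would be zero.

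**4. Size at component level.** Take 1% incidence and 20% with shift, again assumed. Cases: 506 × 0.01 = 5.06. Counted: 5.06 × 0.20 = 1.01. Probability that none is counted: (1 − 0.002)^506 = 0.36. About five air leaks would then appear as one, with roughly a one-in-three chance of appearing as none.

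**The case against.** A reader might infer that most barotrauma from the maneuver is scored as no event and that the error runs in one direction, towards the experimental strategy. The article does not support that, for four reasons.

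- **Other components catch many cases.** A pneumothorax that lowers saturation to the stated thresholds, or that leads to more FiO2, more CPAP, ventilation or reintubation, is still a primary event. This stands, with limits. Scheduled air tests end 180 minutes after PACU admission while the composite runs for 7 days (assessments on days 1, 2 and 7 could still find hypoxemia). Drain insertion counts nowhere. A case recorded as hypoxemia is not identified as an air leak.
- **The word *most* needs a share with shift that the article does not give.** This stands.
- **The direction is conditional.** The definition is the same in all arms, and an under-count favours the individualized arms only if the maneuver raises incidence there. Positive pressure is also used elsewhere: one standard arm receives postoperative CPAP, and CPAP or noninvasive ventilation is part of rescue in every group. This stands.
- **Strict radiological criteria are not peculiar to this entry.** Atelectasis and pleural effusion also require displacement of structures, and strict atelectasis criteria could, on the trial's own hypothesis, drop events mainly from the standard arms. This argues against a selective choice. It does not restore the lost pneumothorax cases.

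A reader might also see a contradiction with the exclusion criterion, which bars patients with any pneumothorax on radiograph or CT and asks for no shift. That is an eligibility rule and not an outcome definition, and a broad exclusion can coexist with a stricter endpoint. It shows only that the broader meaning is already in use in the trial.

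**Conclusion.** The point holds in a limited form. As written, a confirmed pneumothorax without mediastinal shift does not count under its own component, and it reaches the composite only by meeting another one. Because recruitment maneuvers to 40 cmH2O belong only to the two individualized intraoperative arms, this weakens the component exactly where it would inform on harm.

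The effect on the primary contrast is small: 0.025 to 2.0 percentage points under the assumed ranges, against a planned 12.5, and the top of that range requires 2% incidence, no case with shift, no capture by other components and no loss in the comparator. The primary test is unlikely to turn on it, and nothing shows that the interim test at P < 0.001 would be materially affected. Bias towards the individualized arms is possible but not established. The main loss is in the reported pneumothorax rate by arm and in what can be concluded from it about safety.

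**What to change.** Define the component as any radiologically confirmed air in the pleural space, with or without mediastinal shift, applied identically in all four arms. Record shift and drain insertion as severity descriptors, so that the narrower category can still be reported.

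The cost is one line in the outcome definition and a small addition to the e-CRF. No extra imaging is needed. The reported pneumothorax rate may rise slightly. Because imaging is prompted by suspicion, the change will not find unsuspected cases; it only ensures that a pneumothorax already seen on a film is counted.

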### Other follow-up variables

Baseline variables will be recorded preoperatively and are age, sex, height, weight, body mass index, American Society of Anesthesiologists (ASA) physical status, sequential organ failure assessment (SOFA) score, ARISCAT [26] risk score, type of intervention, and medical history.

Intraoperative parameters recorded at three different time points (post-induction, 60 min after induction, and pre-extubation) will be: arterial blood gases, SpO_2_, FiO_2_, respiratory variables [VT, PEEP, P_aw_, P_plat_, C_rs_, respiratory system resistance (R_aw_), hemodynamics (cardiac index, PAM, and stroke volume variation (SVV) and/or pulse pressure variation (PPV)], diuresis, and temperature. Other relevant data that include the types of anesthetic drugs used, type and volume of fluids, blood loss and transfusion requirements, need of vasoactive drugs, diuresis, nasogastric tube insertion, duration of surgery, mechanical ventilation time, number of recruitment maneuvers performed, and the need for rescue therapy will also be recorded.

### Statistical analysis

The sample size was estimated from the literature, assuming a risk of 25% for developing postoperative pulmonary or non-pulmonary complications [17], a relative reduction of 50% in the incidence of these complications with individualized alternative treatment in the groups, and taking into account the statistical power for making matched comparisons between the four groups in the study [37]; using a significance level of 5% and a power of 80% results in a total requirement of 920 patients (230 in each ventilatory management group). This figure was enlarged to 1012 (10%) to compensate for possible dropouts. The recruitment among centers will be competitive.

First, the patient baseline variables will be described and the homogeneity of these groups evaluated using appropriate statistical tests for the type of variable being analyzed (mean difference of proportions, chi-square, ANOVA, with a corresponding confidence interval of 95%). Then bivariate associations between patient characteristics, the primary endpoint, and the secondary outcomes will be performed by calculating their respective odds ratios or, in the case of a quantitative outcome, by an ANOVA test.

Following this, the association between the intervention groups and the main and secondary outcomes will be analyzed, calculating the corresponding odds ratio, or ANOVA in the case of quantitative outcomes. In all cases, respective means or proportions are estimated with their respective 95% confidence intervals. The primary outcome, pulmonary complications outcome, non-pulmonary complications, and mortality measurement analyses will be repeated using multivariate logistic regression models and adjusted to any patient characteristics that are shown to be clinically relevant by the previous bivariate analyses. Similarly, a multilevel analysis will be performed, incorporating different hospitals as random effects in order to assess whether the recruitment center influenced the results.

The monitoring plan is based on the modified Haybittle-Peto boundaries for stopping trials after interim analyses in the second half of the inclusion period [38,39]. Analysis of the main endpoint will be presented to the Data and Safety management board under a blinded code for allocation group. The first interim analysis will be conducted when outcome data of 460 trial participants have been obtained and/or the main endpoints for 150 participants have been documented. If this first interim analysis is significant (*P* <0.001) for benefit or harm from the intervention, a second interim analysis will be carried out when outcome data for 600 trial participants have been obtained. If this second interim analysis is also statistically significant (*P* <0.001) for benefit or harm, the Data and Safety management board will advise the Steering Committee to stop the trial.

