Therefore, iPROVE aims to compare the efficacy of perioperative individualized ventilation and standard lung-protective ventilatory strategies to reduce the overall incidence of a composite of pulmonary and systemic complications.

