### Method of randomization and bias minimization

Informed consent will be obtained from each participant before enrollment in the study. Patients who meet all the inclusion criteria and none of the exclusion criteria will be consecutively included and randomized into one of the four study arms (Figure 1): Individualized perioperative group; Individualized intraoperative group + postoperative CPAP; Standard intraoperative group + postoperative CPAP; Standard perioperative group.

The patients will be randomized online via the website http://iprove.incliva.es using the Mersenne Twister algorithm with an allocation rate of 1:1:1:1.

Blinding: At least two investigators are required in each participating center, because the study characteristics do not allow the blinding of investigators in the operating and postoperative room, so data acquired in these sites will not be blinded. After 24 h, all data will be acquired by the second investigator who will be blinded to the randomization arm.

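### The 230 per group implies a correction for six pairwise comparisons that the stated analysis does not carry through, and no confirmatory contrast is named among the four arms

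*Protocol article*

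**What the plan says.** All the sizing inputs are in the Statistical analysis section of the protocol article. It starts from "assuming a risk of 25% for developing postoperative pulmonary or non-pulmonary complications", posits "a relative reduction of 50% in the incidence of these complications with individualized alternative treatment in the groups", and adds that the calculation was made "taking into account the statistical power for making matched comparisons between the four groups in the study". The result is that "using a significance level of 5% and a power of 80% results in a total requirement of 920 patients", with "230 in each ventilatory management group". Allocation is equal across the four arms (Method of randomization and bias minimization).

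The analysis paragraphs of the same section say that the effect of group on the main and secondary outcomes will be expressed as odds ratios, or by ANOVA for quantitative outcomes. The only confidence level given there is in this sentence: "In all cases, respective means or proportions are estimated with their respective 95% confidence intervals". No reference arm, primary contrast, adjusted level or testing order appears.

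The aim at the end of the Background is narrower: "iPROVE aims to compare the efficacy of perioperative individualized ventilation and standard lung-protective ventilatory strategies". The end of the Discussion likewise ties the trial's conclusion to the individualized perioperative approach. The interim rule, at the end of the Statistical analysis section, acts on P < 0.001 for benefit or harm of the intervention, in the singular, in a trial with three alternatives to the standard arm.

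**The concern.** The sizing and the analysis seem to answer different questions. The sample size looks as though it pays for a correction over every pair of arms, the aim describes one contrast, and the analysis text commits to neither. Four arms give six odds ratios for the primary outcome.

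If nothing fixes which of them decides the trial, or at what level, a positive claim could rest on whichever contrast happens to fall below 0.05, with a family-wise error well above the printed 5%. The data and safety board has the same difficulty, because its stopping rule does not say which comparison supplies the P value.

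**Working it through.** **Inputs.** From the Statistical analysis section: p1 = 0.25; p2 = 0.25 × 0.5 = 0.125; level 5%; power 80%; 230 per group. Assumptions, since the text does not say: two-sided tests, and the phrase about matched comparisons read as pairwise comparisons. Four groups give 4 × 3 / 2 = 6 pairs.

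**Step 1: reproduce 230.** With the unpooled formula,

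n = (z(1−α/2) + z(0.80))² × [p1(1−p1) + p2(1−p2)] / (p1−p2)².

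The variance sum is 0.1875 + 0.109375 = 0.296875. Divided by 0.125² = 0.015625, this is 19.0.

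- α = 0.05: (1.960 + 0.842)² × 19 = 149.1 per group.
- α = 0.05/3: about 199 per group.
- α = 0.05/6 = 0.00833: (2.638 + 0.842)² × 19 = 230.1 per group.

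Other versions of the formula, rounded up:

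| Level per comparison (two-sided, 80% power) | Unpooled | Pooled | Continuity-corrected |
|---|---|---|---|
| 0.05 | 150 | 152 | 168 |
| 0.05/3 | 199 | 203 | 219 |
| 0.05/6 | 231 | 235 | 251 |
| Šidák for 6 | 230 | 234 | 250 |

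No version at an unadjusted 5% comes near 230. Two other combinations do come close: 0.05/5 pooled (227) and 0.05/4 with continuity correction (232). But neither five nor four is the number of pairs among four groups, and six is. The printed 5% is therefore best read as a family-wise level, spent at about 0.0083 per comparison.

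**Step 2: power at 230 per group for 25% versus 12.5%.** Unpooled, √(230/19) = 3.479.

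- At 0.05/6: 3.479 − 2.638 = 0.841, power 80.0% (pooled formula 79.0%).
- At 0.05: 3.479 − 1.960 = 1.519, power 93.6% (pooled formula 93.2%).

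**Step 3: family-wise error if all six pairs were tested at an unadjusted 5%.** With no true differences, at least one pair is significant when the studentized range for four groups exceeds 1.960 × √2 = 2.772. That probability is 20.3%. Simulation with 230 per group gives 20.2% at a common risk of 25% and 20.6% at 12.5%. The independence formula, 1 − 0.95⁶ = 26.5%, overstates it because the pairs share arms. With each pair at 0.05/6, simulation gives about 4.2%.

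**The case against.** The strongest defence is that the article never says six tests will be run at 5%. The 95% sentence concerns means and proportions and is not a decision rule for odds ratios. Neither six nor 0.05/6 is printed. The sizing sentence shows that multiplicity was considered, and an adjusted level or a testing order may stand in an analysis plan that is not shown. The Background and Discussion also indicate which contrast matters.

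Much of this stands. A reader might infer that every contrast will be reported at 5%; the text does not establish that, so the 20% is conditional. What the defence does not remove is that the article prints a level which does not give its own sample size, and describes an analysis that does not use the level which does. Nor does pointing at a contrast in the aim make it the confirmatory one when the sizing is built on comparisons among all four groups.

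A reader might also infer that the stated 80% power fails for most of the six pairs. The documents do not support that. For the only effect they state, power is 79–80% at 0.05/6 and higher at 5%. They give no rate for each arm. If both arms with individualized intraoperative ventilation were at 12.5% and the other two at 25%, four of the six pairs would carry the full effect. If one arm or three arms were at 12.5%, three would, and the remaining pairs would be true nulls with no power to lose. Low power for the component contrasts follows only from intermediate rates that one would have to assume.

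**Conclusion.** The point holds as a mismatch between sizing and analysis. The 230 per group corresponds to about 0.0083 per comparison, against about 150 per group for the printed 5% taken at face value. The stated analysis applies no such level and names no confirmatory contrast. If all six pairs were read unadjusted at 5%, the family-wise error would be about 20%; this is a risk left open by the wording, not a rule the article states. The inference to six comparisons rests on two-sided tests and standard formulas, and is close but not printed. Power for the stated effect is adequate under either reading. The matter goes beyond missing detail because the choice of level and contrast changes what the trial can conclude, and the sample size already covers either choice.

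**What to change.** Keep N and amend the Statistical analysis section, before any comparison by arm is seen:

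1. State that the 80% power applies to one pair of groups differing 25% versus 12.5%, tested two-sided at about 0.0083.
2. Choose one of two rules for the primary outcome:
   - judge all six pairwise comparisons at 0.0083 with 99.2% intervals, the level the sample size already buys; or
   - name individualized perioperative versus standard perioperative as the single confirmatory contrast at 5% (about 93% power at 230 per group), with the other contrasts secondary. This fits the stated aim better.
3. Say which contrast supplies the P value for the interim P < 0.001 rule, consistent with the choice in item 2.

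The cost is wording, with no added patients. The first rule gives wider intervals; under the second, the contrasts that separate the intraoperative and postoperative components have only secondary status.

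### The markers are compared by ANOVA with no baseline covariate although preoperative samples are taken; adjusting for them would add precision at no cost, and how death enters length of stay should be stated

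*Protocol article*

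**What the plan says.** The Statistical analysis section of the protocol article covers the comparison of arms on main and secondary outcomes in one sentence: "calculating the corresponding odds ratio, or ANOVA in the case of quantitative outcomes". It then sets the summary measure: "In all cases, respective means or proportions are estimated with their respective 95% confidence intervals".

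Two further analyses follow, and neither is said to bring in a preoperative marker value:

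- The covariate-adjusted analysis is logistic and restricted to a list: "The primary outcome, pulmonary complications outcome, non-pulmonary complications, and mortality measurement analyses will be repeated using multivariate logistic regression models". Markers and length of stay are not on it.
- The second adds only the hospital: "a multilevel analysis will be performed, incorporating different hospitals as random effects".

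Among the secondary outcomes, the Study variables section lists "The presence of plasma inflammatory markers: increased expression of interleukin 8 (IL-8" together with TNF-α and MCP-1, and states "Plasma samples will be taken preoperatively and 48 h post-surgery". It also lists "Increased ICU length of stay (LOS). Increased hospital LOS". Mortality at 30, 180 and 365 days is a separate outcome. The article gives no rule for a patient who dies in hospital when length of stay is analyzed.

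**The concern.** The trial draws a preoperative sample for each marker, but the stated comparison of arms has no place for it as a covariate. A marker level before surgery usually predicts the level two days later to some degree. Leaving that information out widens the confidence intervals on the outcomes that bear most directly on the inflammatory mechanism described in the article's Background and Discussion.

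The wording of the marker outcome adds to the difficulty. It could mean the 48 h level, the change from the preoperative sample, or a yes/no rise. These are different quantities with different precision, and the article does not choose among them.

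Length of stay raises a smaller question. ANOVA on means needs one number per patient, and a patient who dies in hospital has no time of discharge alive. If the stay simply ends at death, early deaths shorten an arm's mean.

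**Working it through.** **The plan's own figure.** The article gives no standard deviation, correlation, expected stay or mortality, and no sample size for any quantitative outcome. Its one sample-size figure is 230 per arm for the binary primary outcome. Using 25% against 12.5%, 80% power and a two-sided level of 0.05/6 (reading the between-group comparisons as six pairwise tests, which is an assumption), the unpooled formula gives

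(2.638 + 0.842)² × (0.25×0.75 + 0.125×0.875) / 0.125² ≈ 230.1.

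So the figure reproduces. It does not depend on how markers or length of stay are analyzed.

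**Markers.** Let r be the correlation between preoperative and 48 h level, with equal variances at the two times. Taking the variance of the between-arm difference in 48 h level as 1:

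- ANOVA on the 48 h level: 1
- ANOVA on the change: 2(1 − r)
- ANCOVA of the 48 h level on the preoperative level: 1 − r²

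The variance of ANOVA relative to ANCOVA is therefore 1/(1 − r²) on the level and 2(1 − r)/(1 − r²) = 2/(1 + r) on the change. The documents give no r, so the range is assumed.

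| r | 1 − r² | ANOVA on level ÷ ANCOVA | ANOVA on change ÷ ANCOVA |
|---|---|---|---|
| 0.1 | 0.99 | 1.01 | 1.82 |
| 0.2 | 0.96 | 1.04 | 1.67 |
| 0.3 | 0.91 | 1.10 | 1.54 |
| 0.5 | 0.75 | 1.33 | 1.33 |
| 0.7 | 0.51 | 1.96 | 1.18 |

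These ratios are also sample-size equivalents. In terms of power, a two-arm comparison at the 5% level that has 80% power by ANOVA on the 48 h level would have Φ((1.960 + 0.842)/√(1 − r²) − 1.960) with ANCOVA. That is about 84%, 90% and 98% at r = 0.3, 0.5 and 0.7.

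Two features of the table matter. ANCOVA is at least as precise as either form of ANOVA at every r shown. And since 2(1 − r) exceeds 1 when r is below 0.5, analyzing the change is then less precise than not using the preoperative value at all.

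**Length of stay.** Suppose that stay is counted to discharge or death, whichever comes first. An arm with more in-hospital deaths then has its mean shifted by

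−(excess risk of in-hospital death) × (mean stay of survivors − mean stay of those who die).

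Both terms are assumed:

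- smallest: 0.01 × 4 days = 0.04 days
- largest: 0.03 × 8 days = 0.24 days

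The sign reverses if patients who die have longer stays than survivors.

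**The case against.** **The plan need not ignore the preoperative value.** A reader might infer from the ANOVA wording that it does. The article does not support that as a certainty: its outcome is worded as an increase, and paired samples are taken. A change score would use the preoperative level. A yes/no rise would be analyzed by odds ratio rather than ANOVA. This objection stands against the stronger reading. It does not remove the point, because ANOVA on change is also less precise than ANCOVA at every correlation in the range, and a yes/no rise discards information on the size of the change.

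**The plan does not say that death counts as a short stay.** This too is tempting to infer, but no sentence says so. A rule for deaths is commonly left to the full protocol or analysis plan, which are not shown. The direction of any distortion is also an assumption, since a patient may die after a long, complicated course. Mortality is reported separately, so an excess of deaths would be visible. All of this stands, which is why the length-of-stay point is only conditional. What remains is that the remedies suited to death as a competing event are not ANOVA on means, so a later rule alone might not fit the method already stated.

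**Skewness does not invalidate the test.** With four lognormal arms of 230 and no true difference, simulated type I error of ANOVA at a nominal 5% was about 5%, 5% and 4% for log-scale standard deviations of 0.7, 1.0 and 1.5. The case for the log scale therefore rests on precision and interpretation.

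**The gain may be small.** At correlations of 0.1 to 0.2 the ratio on the 48 h level is only 1.01 to 1.04. That is correct, and nothing in the documents favors the upper end of the range.

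**Conclusion.** The point holds as a free gain in precision on secondary outcomes. The article fixes ANOVA on means and names no baseline covariate for markers that it measures before surgery. Relative to ANCOVA the variance is 1.10 to 1.96 times as large on the 48 h level, or 1.54 down to 1.18 times on the change, as the assumed correlation runs from 0.3 to 0.7. These figures assume equal variances at the two times and a correlation on whatever scale is analyzed.

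It is not a finding of bias: ANOVA on either the 48 h level or the change is unbiased under randomization.

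The length-of-stay part is secondary. It applies only if stay is cut off at death and patients who die have shorter stays. Even then the shift is about 0.04 to 0.24 days for 1 to 3 percentage points of excess deaths and stays 4 to 8 days shorter. The primary outcome and the sample size are not touched.

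**What to change.** 1. Define each marker outcome as the 48 h level. Compare arms by ANCOVA of the log 48 h level on the log preoperative level and arm, with center in the model, and report ratios of geometric means with 95% confidence intervals.
2. State how an in-hospital death enters ICU and hospital length of stay, and match the method to it: either time to discharge alive with death as a competing event, or a rank comparison with death as the worst result.

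Both are changes of wording in the analysis section, to be made before anyone sees results by arm. They need no extra samples, patients or follow-up. The sample size and the primary analysis stay as they are.
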